# Study protocol of an open-label, single arm phase II trial investigating the efficacy and safety of Trifluridine/Tipiracil combined with irinotecan as a second line therapy in patients with cholangiocarcinoma (TRITICC)

**DOI:** 10.1186/s12885-023-10972-6

**Published:** 2023-05-22

**Keywords:** Chemotherapy, Biliary tract cancer, Cholangiocarcinoma, FTD/TPI (Trifluridine/Tipiracil), Gall bladder carcinoma, Irinotecan, Second-line treatment, Translational research

## Abstract

**Background:**

The prognosis of patients with advanced biliary tract cancer (BTC) who have progressed on gemcitabine plus cisplatin is dismal. Trifluridine/tipiracil (FTD/TPI) and irinotecan have proven efficacy in different gastrointestinal malignancies. We therefore hypothesized that this combination might improve the therapeutic outcome in patients with BTC after failure of first line treatment.

**Methods:**

TRITICC is an interventional, prospective, open-label, non-randomised, exploratory, multicentre, single-arm phase IIA clinical trial done in 6 sites with expertise in managing biliary tract cancer across Germany. A total of 28 adult patients (aged ≥ 18 years) with histologically verified locally advanced or metastatic biliary tract cancer (including cholangiocarcinoma and gallbladder or ampullary carcinoma) with documented radiological disease progression to first-line gemcitabine based chemotherapy will be included to receive a combination of FTD/TPI plus irinotecan according to previously published protocols. Study treatment will be continued until disease progression according to RECIST 1.1 criteria or occurrence of unacceptable toxicity. The effect of FTD/TPI plus irinotecan on progression-free survival will be analyzed as primary endpoint. Safety (according to NCI-CTCAE), response rates and overall survival are secondary endpoints. In addition, a comprehensive translational research program is part of the study and might provide findings about predictive markers with regard to response, survival periods and resistance to treatment.

**Discussion:**

The aim of TRITICC is to evaluate the safety and efficacy of FTD/TPI plus irinotecan in patients with biliary tract cancer refractory to previous Gemcitabine based treatment.

**Trial registration:**

EudraCT 2018–002936-26; NCT04059562

## Background

Biliary tract cancer (BTC) represents a heterogeneous group of malignant tumours that may arise at any point of the biliary tree [1]. Despite being rare tumors, the global incidence of BTC is rising, currently accounting for ~ 15% of all primary liver cancers and ~ 3% of gastrointestinal malignancies [1]. In Germany about 5,000 BTC are newly diagnosed per year [2, 3]. The “silent” presentation of BTC combined with their highly aggressive nature and refractoriness to chemotherapy contribute to their alarming mortality, representing ~ 2% of all cancer-related deaths worldwide yearly [1].

The ABC-02 study established cisplatin and gemcitabine as first-line treatment in patients with advanced biliary tract cancer and represented the standard of care for many years [4]. Recently, the TOPAZ-1 trial demonstrated improved overall survival with durvalumab in combination with cisplatin and gemcitabine versus chemotherapy alone [5]. However, after failure of first-line treatment, many patients experience a rapid decline in performance status and only 15–25% receive second-line chemotherapy [6, 7]. Therefore, the role of second-line cytotoxic chemotherapy after progression on cisplatin and gemcitabine has remained unclear until now. A systematic review and meta-analysis of phase II data recently provided evidence for second-line chemotherapy to prolong median progression-free (PFS) and overall survival (OS) [8]. Walter and colleagues provided strong evidence that the efficacy of combination therapies is significantly higher compared to monotherapies in BTC-patients refractory to a first line therapy [6]. In a phase-3 study, second-line FOLFOX versus active symptom control alone demonstrated a moderate but significant improvement of survival and might be regarded as a standard of care [9] A potential alternative might be the addition of irinotecan or nanoliposomal pegylated irinotecan to fluoropyrimidines—a combination that also improved survival in a randomized Korean study [10]. Therefore, it might be concluded that available second-line evidence comprises doublet regimens with platinum and irinotecan, both in combination with fluoropyrimidines that are based on limited evidence and questionable generalizability. Thus, there is a high need for novel treatment concepts in patients without targetable genetic alterations [11].

Trifluridine/tipiracil (Lonsurf(®)) is a novel, orally active, antimetabolite agent comprised of trifluridine, a thymidine-based nucleoside analogue, and tipiracil, a potent thymidine phosphorylase inhibitor. Trifluridine is incorporated into DNA via phosphorylation, ultimately inhibiting cell proliferation. Tipiracil increases systemic exposure of trifluridine when coadministered [12].Trifluridine/tipiracil has recently been approved for the treatment of adult patients with metastatic colorectal cancer (mCRC) who are refractory to, or are not considered candidates for, current standard chemotherapy [13] and in gastric cancer after failure of standard treatments [14]. Notably, FTD/TPI proved efficacy in patients with 5-FU resistance [13, 15]. Recently, in a nicely conducted phase II study, FTD/TPI demonstrated promising antitumor activity with acceptable toxicity in heavily pretreated patients with advanced BTC [16]. Moreover, in a recently published single arm phase II trial comprising 28 patients (27 evaluable) with advanced BTC, the combination of trifluridine/tipiracil plus irinotecan showed promising safety and activity (ORR 20% and DCR 45%, 16-week PFS 37% and median OS 52,6 weeks, respectively) [17]. Moreover, in a recent randomized trial analyzing a total of 120 patients it turned out that mFOLFIRI was tolerable and showed comparable efficacy to mFOLFOX in the second-line treatment of BTC [18], supporting a deeper analysis of the combination of trifluridine/tipiracil plus irinotecan in further clinical trials.

## Objectives and endpoints

### Objectives

The primary objective of the TRITICC trial is to examine the efficacy of a combination therapy of FTD/TPI and Irinotecan in patients with advanced, non resectable or metastatic BTC after failure to respond to a previous gemcitabine based treatment. Secondary objectives are to determine the efficacy and safety of the treatment concept, health-related quality of life (HR-QoL) and translational investigation.

### Endpoints

The primary endpoint is median progression free survival (PFS) assessed by the local investigator. Secondary endpoints are Progression-free survival rate @ 4 months, median overall survival and proportion of patients with an objective response according to RECIST 1.1 [19]. Secondary safety endpoints are type, grade, frequency and severity of adverse events according NCI CTCAE version 5.0. Secondary endpoint quality of life will be assessed by EORTC QLQ-30 and the EQ-5D-5Lquestionnaires. Secondary translational endpoints are cfDNA exome sequencing, circulating miRNAs and lncRNAs, concentrations of inflammatory cytokines and gut microbiome analysis. (Table 1).

**Table 1 Tab1:** Objectives and endpoints of the TRITICC trial

**1. Objectives**
**1.1 Primary Objectives** • To assess the efficacy of a combination therapy of FTD/TPI and Irinotecan in patients with advanced, non resectable or metastatic cholangio- and gallbladder carcinoma after failure to respond to a previous gemcitabine treatment.
**1.2 Secondary Objectives** • To determine efficacy and safety of the treatment concept • To determine health-related quality of life (HR-QoL) • To determine translational observations (circulating miRNAs and lncRNAs, concentrations of inflammatory cytokines, gut microbiome analysis)
**2. Endpoints**
**2.1 Primary Endpoint** • Median progression free survival (PFS) assessed by the local investigator
**2.2 Secondary Endpoints**
**Efficacy** • Progression-free survival rate @ 4 months defined as the proportion of patients with non-progressive disease 4 months after inclusion by intention to treat analysis • Median overall survival • Proportion of patients with an objective response according to RECIST 1.1

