### Statistical considerations

The primary endpoint, time till progression-free survival, will be analyzed using a non-parametric survival estimate. To this end the method of Turnbull will be used to compute the survival curve [22]. The variance of the survival will be estimated using the Greenwood formula. The log transformation will be used for the calculation of confidence intervals.

An exploratory analysis of secondary outcomes will be performed. Overall survival will be analyzed using the Kaplan–Meier estimate of survival. For the secondary outcomes, objective response and occurrence of adverse events the proportion of patients with the outcome and confidence intervals using the Wilson method will be calculated [23].

The statistical analysis will be carried out by the Coordination Center for Clinical Trials Düsseldorf (KKSD).

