### Sample size determination

Sample size consideration for this study is based on the precision of the survival estimate for the outcome progression-free survival. Based on previous results with the combination of Irinotecan and 5-FU therapy in patients with biliary tract cancers we assume a median survival time of 3 months. Assuming an exponential failure time with a median survival of 3 months (hazard rate: 0.23 per month) and a censoring rate of 0.04 per month, a total sample size of 28 patients (including 3 calculated drop outs and invalid cases) results in an expected standard error of 0.09 for the 3 months survival.

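### The 4-month PFS rate is defined as an intention-to-treat proportion, which cannot properly handle patients censored before month 4

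*Protocol article*

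**What the plan says.** Table 1 (2.2 Secondary Endpoints, Efficacy) gives the 4-month PFS rate its own definition: "defined as the proportion of patients with non-progressive disease 4 months after inclusion by intention to treat analysis". It has no rule for patients whose status at month 4 is unknown, and it does not mention death.

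The primary endpoint concerns the same outcome: "The primary endpoint is median progression free survival (PFS) assessed by the local investigator". Statistical considerations treats it as time-to-event data: "The primary endpoint, time till progression-free survival, will be analyzed using a non-parametric survival estimate", and "To this end the method of Turnbull will be used to compute the survival curve". Variance is by Greenwood's formula, with log-transformed confidence limits.

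Sample size determination assumes exponential failure with a median of 3 months, "and a censoring rate of 0.04 per month", and 28 patients, 3 of whom are allowed for as drop-outs or invalid cases.

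Among secondary outcomes, Statistical considerations assigns Kaplan-Meier to overall survival. Wilson intervals are for "objective response and occurrence of adverse events the proportion of patients with the outcome and confidence intervals using the Wilson method will be calculated". No estimator is named for the 4-month PFS rate.

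**The concern.** One outcome is handled in two ways. The PFS curve uses a censored patient's information up to the last assessment and no further. A proportion with all enrolled patients in the denominator must count that patient as a success or a failure. Either choice shifts the result, and the definition does not say which is meant. An analysis plan that followed Table 1 literally would inherit the problem.

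At stake is one descriptive figure. In a single-arm trial, though, readers will set a 4-month PFS rate beside outside results, and they may find that it does not match the value at month 4 on the trial's published curve.

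**Working it through.** **The plan's own figure.** The article states no expected value for the 4-month rate, so there is nothing to reproduce directly. The nearest figure is the standard error of 0.09 for 3-month PFS. The stated inputs give 0.098 with 28 patients and 0.103 with 25. That mismatch is a separate matter and does not enter below.

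**Inputs** (Sample size determination):
- event hazard h = ln 2 / 3 = 0.231 per month (0.23 in the article)
- censoring rate c = 0.04 per month, so h + c = 0.271
- n = 28; t = 4 months

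**Step 1. True 4-month PFS.** S(4) = exp(−4h) = exp(−0.924) = 0.397.

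**Step 2. Status of patients at month 4**, with event and censoring as competing exponentials:
- known event-free: exp(−4(h + c)) = exp(−1.084) = 0.338, or 9.5 of 28
- censored event-free before month 4: [c/(h + c)] × (1 − 0.338) = 0.1476 × 0.662 = 0.098, or 2.7 of 28
- event observed: [h/(h + c)] × (1 − 0.338) = 0.8524 × 0.662 = 0.564, or 15.8 of 28

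**Step 3. The proportion under each rule:**

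| Patients censored before month 4 | Expected proportion | Difference from 39.7% |
|---|---|---|
| counted as failures | 0.338 | −5.9 points |
| counted as non-progressive | 0.338 + 0.098 = 0.436 | +3.9 points |
| left out of the denominator (not intention to treat) | 0.338 / (1 − 0.098) = 0.375 | −2.2 points |

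**Step 4. Size against sampling error.** The Greenwood-type variance is S(t)² × [h/(h + c)] × [exp((h + c)t) − 1] / n. At t = 4 it gives a standard error of 0.097 with n = 28 and 0.103 with n = 25. Both intention-to-treat deviations are below one standard error.

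**Step 5. How often the two figures differ.** In 20,000 simulated trials of 28 patients, the mean Kaplan-Meier estimate at month 4 was 0.397. The mean proportion with censored patients as failures was 0.338. They agreed only when nobody was censored before month 4, in about 5.5% of trials. Event times were taken as exactly observed, so Kaplan-Meier stands in for Turnbull.

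**Step 6. A lower censoring rate.** Suppose, as an assumption, that the rate is half the planned one, c = 0.02. The known event-free share is exp(−4 × 0.251) = 0.366. The censored share is (0.02/0.251) × 0.634 = 0.050, or 1.4 of 28. The proportion is then 0.366 (−3.1 points) or 0.417 (+2.0 points). The gap shrinks roughly in step with the censoring rate.

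**The case against.** **The crude reading is an inference.** Table 1 defines an endpoint and names no estimator, Wilson intervals are not assigned to it, and a full protocol or analysis plan may settle the method. This stands in part: what is shown is the effect of following the printed definition literally. A proportion of all patients by intention to treat is still its natural reading, and nothing in the article reconciles it with the curve.

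**Counting unknown patients as failures is a recognised conservative convention.** True, but the article does not state it. It deserves a place as a sensitivity figure.

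**The planned censoring may overstate losses before month 4.** Recruitment from Q3 2021 for 18 months, with the last visit in August 2023, gives the last patient about five months or more. Administrative censoring before month 4 is therefore not expected. The article does not say what makes up the 0.04, or whether it overlaps with the 3 drop-outs and invalid cases. This stands, and it is why the conclusion says probable and not certain.

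**The curve is not perfect.** It assumes non-informative censoring, which may fail if declining patients drop out. A Turnbull estimate is also not unique inside an interval between assessments, and month 4 could fall in one. Both stand as small costs of the fix.

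**Stronger readings that the documents do not support:**
- A reader might infer that the definition misclassifies deaths. It is only silent on them. A patient who has died would not naturally be called a patient with non-progressive disease at month 4. If a share d of events were deaths without progression and were counted as non-progressive, the rate would rise by 0.564 × d: 2.8 points at d = 5%, 11.3 points at d = 20%. Those shares are assumptions, and nothing shows that deaths would be counted that way.
- A reader might quote the distance from 33.8% to 43.6% as a 10-point error. It is the distance between two opposite rules and not the error of either.
- A reader might say that the choice decides the comparison with the 16-week PFS of 37% cited in the Background. The article does not say how that figure was computed.

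**Conclusion.** The point holds for censoring. As printed, the 4-month PFS rate is an intention-to-treat proportion without a proper way to treat patients censored before month 4. Its expected value is 5.9 points below or 3.9 points above the true 39.7%, depending on an unstated rule, and it would probably disagree with the trial's own PFS curve.

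This rests on exponential failure with a 3-month median, independent censoring at 0.04 per month, and a literal reading of Table 1. The treatment of death is unclear but not shown to be wrong. The consequence is limited to a secondary, exploratory endpoint. The primary analysis and the sample size are unaffected.

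**What to change.** Define the 4-month PFS rate in Table 1, and in the analysis plan, as the estimate at 4 months from the same PFS curve as the primary endpoint, with its confidence interval. State that all enrolled patients are included and that progression or death, whichever comes first, is the event. Report the crude proportion, with patients unassessed at month 4 counted as failures, as a sensitivity figure. It also gives a check that does not depend on non-informative censoring. Add how the value is reported if month 4 falls inside an interval where the Turnbull estimate is not unique, for example by giving the values at both ends.

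The cost is a sentence or two of text. No new data, visits or patients are needed.

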**Safety** **• Type, frequency and severity of adverse events with severity according to NCI CTCAE version**
**Health-Related Quality of Life** • HR-QoL according to EORTC QLQ-C30 and the EQ-5D-5L
**Translational part** • **cfDNA exome sequencing**: a panel of 28 mutations (e.g. IDH1, IDH2, SMAD4) that are specific for BTC will be recapitulated in patient’s serum by using cfDNA exome sequencing. • **Circulating miRNAs and lncRNAs**: Alterations in serum miRNAs as prognostic markers will be analysed using array based techniques in representative patients and significantly altered miRNAs will be validated using qPCR in the whole cohort of patients. • Concentrations of inflammatory cytokines: A panel of inflammatory cytokines will be analyzed using FACS bead technology in the serum of patients. This panel will include analysis of Osteopontin, suPAR, APRIL, TWEAK, TRAIL, CCL1, 2, 5, and CXCR1, 2, 5, 9) • **Gut microbiome analysis:** By using high-throughput sequencing of bacterial 16S RNA a complete and unbiased analysis of the gut microbiota will be performed in each individual patient. Both the baseline composition and alterations during therapy will be correlated with PFS and response to therapy.

## Methods/study design

TRITICC is an interventional, prospective, open-label, non-randomised, exploratory, multicentre, single-arm phase IIA clinical trial organized and sponsored by the University of Dusseldorf. Eligible patients with histologically or cytologically confirmed, non-resectable, locally advanced or metastatic cholangiocarcinoma or gall bladder carcinoma will receive a second line combination chemotherapy with FTD/TPI and irinotecan in cycles of 14 days. In total 28 patients (including 3 calculated dropouts and invalid cases) after failure of a gemcitabine based first-line therapy will be enrolled at up to 6 centers. Screening is expected to be necessary in 40 patients.

### Study duration

The recruitment of patients for the inclusion of the study was started in Q3 2021. The recruitment period will last 18 months. Patients will be treated until radiological progression. In average this is estimated being about 4 months. A follow up is planned every 3 months up to 6 months. Last patient last visit is anticipated for August 2023. Based on these assumptions, duration will be in total 40 months including 12 months evaluation and clinical study report.

### Trial population

Patients with cholangiocarcinoma or gall bladder carcinoma after progressing on a gemcitabine based first-line therapy and fulfilling the other inclusion criteria will be eligible to participate in this clinical trial.

### Inclusion criteria

Written informed consent incl. participation in translational research and any locally-required authorization (EU Data Privacy Directive in the EU) prior to performing any protocol-related procedures, including screening evaluationsAge ≥ 18 years at time of study entryHistologically or cytologically confirmed, non-resectable, locally advanced or metastatic cholangiocarcinoma or gall bladder carcinomaMeasurable or assessable disease according to RECISTDocumented disease progression after prior gemcitabine or gemcitabine containing therapy. Examples of permitted therapies include, but are not limited to: a) Single agent gemcitabine); b) Any gemcitabine-based regimen, with or without maintenance gemcitabineECOG performance status 0–1Ability to take medications orallyAdequate blood count, liver-enzymes, and renal function:ANC > 1,500 cells/μL without the use of hematopoietic growth factors; and Platelet count ≥ 100 × 109/L (> 100,000 per mm3) and Hemoglobin > 9 g/dL (blood transfusions are permitted for patients with hemoglobin levels below 9 g/dL)Serum total bilirubin ≤ 1.5 × upper normal limit (ULN) (biliary drainage is allowed for biliary obstruction; elevated bilirubin should be caused by obstruction not impaired liver function as assessed by albumin and INR values):Albumin levels ≥ 3.0 g/dLPatients not receiving therapeutic anticoagulation must have an INR < 1.5 ULN and PTT < 1.5 ULN within 7 days prior to inclusion. The use of full dose anticoagulants is allowed as long as the INR or PTT is within therapeutic limits (according to the medical standard in the institution) and the patient has been on a stable dose for anticoagulants for at least three weeks at the time of inclusion.AST (SGOT) and ALT (SGPT) ≤ 5 × institutional upper limit of normalSerum Creatinine ≤ 1.5 × ULN and a calculated glomerular filtration rate ≥ 30 mL per minute Adequate renal and bone marrow functionIn case of liver cirrhosis: Child–Pugh AWomen of childbearing potential must have a negative pregnancy test and must agree to adequate birth control if conception is possible. Males must agree to adequate birth control

### Exclusion criteria

Age < 18 yearsCNS metastasesActive, uncontrolled infectionAdditional malignancy within the past 2 years (except adequately treated in-situ carcinoma of the cervix or non-melanoma skin cancer)Clinically significant gastrointestinal disorders including bleeding, inflammation, occlusion, or diarrhea > grade 1Any condition or comorbidity that, in the opinion of the investigator, would interfere with evaluation of study treatment or interpretation of patient safety or study resultsKnown hypersensitivity to FTD/TPI or Irinotecan or their componentsMedication that is known to interfere with any of the agents applied in the trialPregnancy or lactating femalePrior partial or total gastrectomyPrevious radio- or radiochemotherapy, previous transarterial chemoembolisation (TACE), radiofrequencyablation (RFA) or selective intraarterial radiotherapy (SIRT) within 3 months prior to inclusion (except radiation for bone metastases)Patients who might be dependent on the sponsor, site or the investigatorPatients who have been incarcerated or involuntarily institutionalized by court order or by the authorities § 40 Abs. 1 S. 3 Nr. 4 AMG.Patients who are unable to consent because they do not understand the nature, significance and implications of the clinical trial and therefore cannot form a rational intention in the light of the facts [§ 40 Abs. 1 S. 3 Nr. 3a AMG].Use of other investigational treatment within 5 half-lives of enrollment is prohibited.

